# Text Messaging Versus Email Messaging to Support Patients With Major Depressive Disorder: Protocol for a Randomized Hybrid Type II Effectiveness-Implementation Trial

**DOI:** 10.2196/29495

**Published:** 2021-10-13

**Keywords:** email messaging, text messaging, supportive, major depressive disorder, randomized trial, mental health, digital health, mobile health, mHealth, patient care, health policy, decision-making, health care resources

## Abstract

**Background:**

Major depressive disorder (MDD) accounts for 40.5% of disability-adjusted life years caused by mental and substance use disorders. Barriers such as stigma and financial and physical access to care have been reported, highlighting the need for innovative, accessible, and cost-effective psychological interventions. The effectiveness of supportive SMS text messaging in alleviating depression symptoms has been proven in clinical trials, but this approach can only help those with mobile phones.

**Objective:**

This paper presents the protocol for a study that will aim to evaluate the feasibility, comparative effectiveness, and user satisfaction of daily supportive email messaging as an effective strategy compared to daily supportive text messaging as part of the treatment of patients with MDD.

**Methods:**

This trial will be carried out using a hybrid type II implementation-effectiveness design. This design evaluates the effectiveness of an implementation strategy or intervention, while also evaluating the implementation context associated with the intervention. Patients with MDD receiving usual care will be randomized to receive either daily supportive email messaging or daily supportive text messaging of the same content for 6 months. The Patient Health Questionnaire-9, the Generalized Anxiety Disorder-7, and the 5-item World Health Organization Well-Being Index will be used to evaluate the effectiveness of both strategies. The implementation evaluation will be guided by the RE-AIM (Reach, Effectiveness, Adoption, Implementation, and Maintenance) framework, as well as the Consolidated Framework for Implementation Research. All outcome measures will be analyzed using descriptive and inferential statistics. Qualitative data will be analyzed using thematic analysis.

**Results:**

Data collection for this trial began in April 2021. We expect the study results to be available within 18 months of study commencement. The results will shed light on the feasibility, acceptability, and effectiveness of using automated emails as a strategy for delivering supportive messages to patients with MDD in comparison to text messaging.

**Conclusions:**

The outcome of this trial will have translational impact on routine patient care and access to mental health, as well as potentially support mental health policy decision-making for health care resource allocation.

**Trial Registration:**

ClinicalTrials.gov NCT04638231; https://clinicaltrials.gov/ct2/show/NCT04638231

**International Registered Report Identifier (IRRID):**

DERR1-10.2196/29495

## Introduction

### Background

Depression is a debilitating condition characterized by changes in mood, self-attitude, cognitive functioning, sleep, appetite, and energy levels [1,2]. Decreases in the quality of life associated with depression leads to impairment in occupational and social functioning [2,3]. In 2010, it was estimated that mental and substance use disorders were the leading cause of years lived with disability worldwide, with depressive disorders accounting for 40.5% of disability-adjusted life years caused by mental and substance use disorders [4]. Depression is thus a major contributor to the overall global burden of disease [4-6], and it is projected by the World Health Organization that major depressive disorder (MDD) will be the leading cause of disability worldwide by 2030 [7].

In 2012, over 3.2 million Canadians over 15 years of age (11.3%) reported symptoms of major depression, which is associated with higher health and service utilization than most other patients [8]. Psychosocial interventions and pharmacotherapy are among preferred first-line treatments for severe mental health problems including major depression [9]. Psychotherapies, such as cognitive behavior therapy, interpersonal psychotherapy, problem-solving, and behavioral activation are common and effective forms of treatment for depression [9]. However, access to these psychotherapies is limited by human resource capacity constraints, which leaves the majority of people with depressive disorders untreated [10,11]. Access is further limited by geographic location as psychosocial services are also more frequently available in cities and towns [12], with far less access for rural inhabitants [13]. Even in cities and towns, these services are mostly only available during the working days and day-time business hours [8,14], with caregivers often dealing with twice the recommended number of clients, further restricting appointment availability [14]. Long wait-times to access counseling services and the stigma associated with seeking mental health counseling also compound the problem. In the 2012 Canadian Community Health Survey on Mental Health, barriers such as lack of a readily available care system, stigma, and affordability of health care services were reported by 2.3 million Canadians, who expressed they had unmet or partially met mental health care needs [15,16]. It is clear that the traditional ways of providing mental health care alone will not be able to meet the demands for services given that the prevalence of depression is so high and not likely to decrease any time soon [17]. Consequently, there is a need to develop innovative psychological interventions that are not human resource intensive, and are easily accessible, cost-effective, independent of geographic location, scalable, and can be offered to thousands of people simultaneously.

Digital technologies for the provision of health care interventions have advanced significantly in the last decade, and further development of this field looks very promising [18]. Current evidence supports the efficacy and cost-effectiveness of these new technologies, such as tele–mental health, as they may enhance access to mental health care and contribute to closing the treatment gap that has existed over the years [19,20]. Useful communication methods for the delivery of mental health services have included smartphone apps, text messages, and email [20,21]. There is therefore a need for the health profession to embrace these new trends of digital technological care, particularly in the domain of mental health [22].

### Intervention and Implementation Strategies

eHealth approaches have been rapidly expanding in recent decades, with evidence indicating that the provision of internet-based mental health services is clinically effective [23] and cost-effective even though many health professionals have, until quite recently, been slow to engage in this clinical domain [24,25]. Supportive text messages have also become increasingly accepted as an appropriate and acceptable means of delivering psychological care to patients with mental health issues [26]. It is estimated that 99% of received text messages are opened, and 90% of all text messages are read within 3 minutes of reception [27], presenting an accessible opportunity to close the psychological treatment gap for patients with depression [28]. In 3 randomized controlled trials conducted in Ireland [29] and Canada [30], patients with MDD who received twice-daily supportive text messages had significantly greater reductions in their depression symptom scores than patients who received treatment as usual. In the first of the 2 studies conducted in Ireland, after 3 months, the mean difference in Becks Depression Inventory-II (BDI-II) scores between the intervention and control groups was –7.9 (95% CI –13.06 to –2.76, Cohen *d*=0.85) in favor of the intervention group [29]. Similar results were reported in another Irish study with a larger sample size and, after 3 months of exposure, a Canadian study reported a significant difference in mean BDI-II scores for the intervention versus control groups (mean 20.8, SD 11.7 vs mean 24.9, SD 11.5, respectively; *F*_1,60_=4.83, *P*=.03, *η*_p_^2^=0.07) with an effect size (Cohen *d*) of 0.67 [30]. A recent literature review of studies conducted on the effectiveness of text messaging as an adjunct therapy for mothers with postpartum depression living in low-income countries also reported a positive outcome [31], where the mothers showed a preference for receiving psychological care via text messaging [32]. Several studies reported high user satisfaction with a supportive text message intervention [28,33], and in one of these studies, 83% of subscribers to the Text4Mood program reported that daily messages contributed to improving their overall mental well-being [28].

Though patronage of supportive text messaging programs is deemed great in most cases due to the high numbers of subscribers, anecdotally, some people were unable to subscribe to supportive text messaging programs such as Text4Hope [33] and Text4Mood [28] because they did not have active mobile phone numbers, including several individuals for whom these programs were recommended by Addiction and Mental Health clinics in Edmonton resulting in inquiries as to whether the messages could be sent to them via email. In the participants’ satisfaction survey for the Text4Hope program, the majority of respondents (64%) were in favor of email messaging as part of their health care support during crisis periods despite having access to mobile phones.

With the rise of eHealth apps, email has been established as a secure avenue of communication, increasingly used for interactions between physicians and their patients [34]. The uniqueness of email messaging can be linked to its special characteristics, including flexibility of message length, asynchronous communication, and rapid message delivery [18]. There is a lack of data on whether email messaging is as effective as text messaging to clinically support patients with MDD.

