### Sample Size

Based on the effect sizes (Cohen *d* of 0.85 and 0.67) achieved in 2 previous randomized trials (n<80 for each trial), which compared daily supportive text messages plus treatment as usual with treatment as usual alone for the management of patients with MDD, a sample size of 80 is estimated to have sufficient power for the current protocol. Allowing for a projected maximal 20% overall dropout rate, we propose to recruit 100 patients with MDD into the trial, with 50 patients randomly allocated into each study arm.

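### The planning effect d = 0.67 does not follow from the statistics printed beside it, which give 0.35 (means and SDs) or about 0.55 to 0.57 (F and partial eta-squared)

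*Protocol article*

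**What the plan says.** The Introduction (Intervention and Implementation Strategies) summarises earlier trials of text messages against usual care.

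- **First Irish trial:** the BDI-II difference in favour of text messages is reported as "7.9 (95% CI –13.06 to –2.76, Cohen *d*=0.85".
- **Canadian trial, 3 months:** text messages versus control are "mean 20.8, SD 11.7 vs mean 24.9, SD 11.5, respectively". The test is "F*_1,60_=4.83, *P*=.03, *η*_p_^2^=0.07", and the sentence ends "with an effect size (Cohen *d*) of 0.67".
- **Second Irish trial:** it is mentioned without figures: "Similar results were reported in another Irish study with a larger sample size".

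The Sample Size section opens "Based on the effect sizes (Cohen *d* of 0.85 and 0.67) achieved in 2 previous randomized trials (n<80 for each trial". It concludes that 80 patients give sufficient power, raised to 100 for 20% dropout. It states no alpha, power or formula.

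The two sections also describe the earlier interventions differently. The Introduction refers to "patients with MDD who received twice-daily supportive text messages", while the Sample Size section calls the messages daily.

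**The concern.** Three descriptions of one comparison stand in a single sentence: means with SDs, a test statistic with its partial eta-squared, and a Cohen d. The d agrees with neither of the other two.

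The figure is also relied on. It is one of only two effect sizes cited for the sample size and, being the smaller, it is the more demanding. If it is too large, the claim of sufficient power rests on an inflated number. Any later noninferiority margin that draws on the text-message effect would inherit the inflation.

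**Working it through.** **Inputs (Introduction, Canadian trial).** Means 20.8 and 24.9; SDs 11.7 and 11.5; F(1,60) = 4.83; P = .03; partial eta-squared 0.07; stated d 0.67. From Sample Size: 80 evaluable, so 40 per arm. Assumed because not printed: two-sided alpha 0.05, and about 63 patients in near-equal arms (60 error degrees of freedom with two groups and one covariate).

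**1. Trying to reproduce 0.67 from the means and SDs.**
- Difference = 24.9 − 20.8 = 4.1.
- Pooled SD = √((11.7² + 11.5²)/2) = 11.60.
- d = 4.1/11.60 = 0.353. Using one arm's SD alone gives 0.350 or 0.357, so the choice of SD does not explain the gap.
- A d of 0.67 would need a difference of 0.67 × 11.60 = 7.8 points, or an SD of 4.1/0.67 = 6.1.

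**2. Trying to reproduce it from the test statistic.**
- Internal check: 4.83/(4.83 + 60) = 0.0745 and P = 0.032, so F, P and eta-squared agree with one another.
- d = 2√(4.83/60) = 0.567.
- With 63 patients in equal arms, d = √4.83 × √(4/63) = 0.554.
- From the printed eta-squared, d = 2√(0.07/0.93) = 0.549.
- Unequal arms raise the result, because d = √F × √(1/n₁ + 1/n₂). Arms of 20 and 43 give 0.59; 0.67 needs about 14 and 49. No arm sizes are printed.

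**3. Are the means and the F on the same footing?** The raw means with 63 patients would give t = 0.353 × √(31.5/2) = 1.40, hence F = 1.97 and P about .17. The printed F is therefore not an unadjusted test of those means. It is probably adjusted for baseline.

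**4. Size of the overstatement.** 0.67/0.353 = 1.9; 0.67/0.567 = 1.18; 0.67/0.549 = 1.22. The range is about 1.2 to 1.9.

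**5. Irish trial as a control.** SE = (13.06 − 2.76)/(2 × 1.96) = 2.63. SD = 7.9/0.85 = 9.29. Implied n per arm = 2 × (9.29/2.63)² ≈ 25, which fits a trial of fewer than 80. This figure is coherent.

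**6. What it does to the sample-size claim.** 80/(1 − 0.20) = 100 reproduces. The 80 cannot be reproduced strictly, since alpha and power are not given. Two-sample t test, two-sided 0.05:

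| d | Source | Power, 40 per arm | n per arm for 80% |
|---|---|---|---|
| 0.85 | Irish, as printed | 96% | 23 |
| 0.67 | Canadian, as printed | 84% | 36 |
| 0.567 | F | 71% | 50 |
| 0.55 | F or eta-squared, lower end | 68% | 53 |
| 0.353 | means and SDs | 34% | 127 |

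So 80 patients fit d = 0.67 on conventional assumptions, but reach 80% power at neither value that the Canadian statistics support.

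**The case against.** The strongest reply is that 0.67 is attributed to a cited trial that is not at hand, and the article does not say whether that d is raw, covariate-adjusted or based on change. It may be right on a scale the sentence does not describe. That stands as far as it goes. The document shows an unreconciled figure and does not prove what the true effect was.

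A reader might therefore go too far in several ways:

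- **That the true effect is 0.35 and the plan simply doubled it.** The printed F does not fit an unadjusted comparison of those means, so 0.35 is the lower end of what the sentence supports, and 1.9-fold the upper end of the overstatement.
- **That 0.57 is a ceiling.** It is not, since unequal arms give a larger d from the same F. Reaching 0.67 would take roughly 14 versus 49, which nothing printed suggests.
- **That this trial has 34% power.** The powers above are for text messages against usual care. The trial tests noninferiority of email to text, and neither 0.67 nor any replacement powers that comparison by itself.
- **That an invalid margin was set from 0.67.** The article states no margin, so there is none to fault.
- **That leaving out the larger Irish trial biased the planning.** No figures for it are printed, so no effect of the omission can be shown.

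It can also be said that the other planning value, 0.85, is sound. That is so, but the section rests on both values, and the smaller is the one that limits the claim.

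**Conclusion.** The point holds in this limited form. The d of 0.67 cannot be obtained from the statistics printed with it. Those support 0.35 on the raw means or about 0.55 to 0.57 on the test statistic, an overstatement of about 1.2 to 1.9-fold. On the section's own superiority logic, power with 40 per arm falls from 84% to about 68 to 71%, or to 34%. The claim of sufficient power is thus not supported at the conventional 80% by either value.

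The non-reproduction from the means needs no assumption. The F-based range assumes near-equal arms, and the powers assume a two-sided 0.05 test. The remaining uncertainty is whether an unprinted definition of d in the cited trial explains 0.67. It should be corrected, because the sample-size rationale leans on the number and the correction is cheap.

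**What to change.** 1. In the Introduction and in Sample Size, either show how 0.67 was derived (raw or adjusted, which SD, arm sizes) or replace it with a labelled value: 0.35 as the raw effect, or about 0.55 to 0.57 as an adjusted effect.
2. Restate the power of 80 patients with that value, giving the alpha and sidedness used. Say that the figure concerns text versus usual care and does not by itself power the noninferiority comparison of email with text.
3. Have any margin that draws on the text-message effect use the corrected figure rather than 0.67.
4. Reconcile the twice-daily description of the earlier trials in the Introduction with the daily description in Sample Size.

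The cost is a text correction and a less favourable stated power. Nothing in data collection changes.

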### Study Aims and Objectives

The *Supportive Text vs Email Messaging* (STEM) trial aims to evaluate comparatively the implementation and impact of two implementation strategies (text messaging and email messaging) for delivering supportive messages to patients with MDD.

The specific objectives are outlined below:

Implementation evaluation:To compare the impact of both strategies for delivering the daily supportive messages on implementation outcomes (adoption, fidelity, reach, cost, sustainability);To evaluate contextual factors that could inhibit or facilitate the implementation of each strategy.Clinical effectiveness evaluation:To compare the mean difference in Patient Health Questionnaire-9 (PHQ-9) [35] scores from baseline and at 6, 12, and 24 weeks for patients with MDD receiving standard care plus daily supportive email messages to those receiving standard care plus daily supportive text messages;To compare the quality of life using the 5-item World Health Organization Well-Being Index (WHO-5) [36] at baseline and at 6, 12, and 24 weeks for patients with MDD receiving standard care plus daily supportive email messages to those receiving standard care plus daily supportive text messages;To compare anxiety levels using the Generalized Anxiety Disorder-7 (GAD-7) scale [37], at baseline and at 6, 12, and 24 weeks, as well as the dropout and satisfaction rates between patients in the two treatment arms.

## Methods

### Study Design

The STEM study design is a mixed methods, hybrid type II implementation-effectiveness trial. This design evaluates the effectiveness of an implementation strategy or intervention, while also evaluating the implementation context associated with the intervention [38,39]. This study is a randomized noninferiority trial testing the outcomes for email messaging (as a strategy for delivering daily evidence-based supportive messages to patients with MDD in addition to usual care), in comparison to outcomes for text messaging, which has been deemed effective by previous studies (with noted implementation limitations [28,33]). The relevant guidelines and checklist were obtained from the Enhancing the Quality and Transparency of Health Research (EQUATOR) network website and used in the design of this trial [40]. These include the SPIRIT (Standard Protocol Items: Recommendations for Interventional Trials) checklist (Multimedia Appendix 1) and CONSORT (Consolidated Standards of Reporting Trials) guidelines (Multimedia Appendix 2) [41,42].

### Study Settings

Patients will be recruited from the Alberta Health Services Access 24/7 clinic located in Edmonton, Canada. This city center Access 24/7 clinic is a zone-wide centralized intake clinic for addiction and mental health. Patients with mental health concerns can self-present or are referred by a primary care provider to the clinic for assessments and referral to other community mental health clinics for follow-up or to other community support services as necessary.

### Participant Recruitment

Patients who have been assessed by a psychiatrist at the Urgent Psychiatric Clinic of the Access 24/7 clinic in Edmonton and diagnosed with an MDD according to the Diagnostic and Statistical Manual of Mental Disorders (DSM-5) criteria using a structured clinical interview will be offered an information leaflet about the study and invited to participate.

### Inclusion Criteria

The inclusion criteria are as follows:

Persons aged 18 to 65 years who have the capacity to provide informed consent;Patients who have been assessed using structured clinical interviews for DSM-5 and diagnosed with an MDD;Patients who have a mobile phone with an active line and a functional email address and can access both email messages and text messages;Patients who willingly agree to be enrolled in the trial and sign the consent form.

### Exclusion Criteria

Patients will be ineligible if they are patients with active psychotic disorders or residing outside of regular mobile phone and internet connection areas. They will also be ineligible if they previously or currently subscribed to Text4Hope, Text4Mood, Text4Support, or another supportive text messaging program.

### Sample Size

Based on the effect sizes (Cohen *d* of 0.85 and 0.67) achieved in 2 previous randomized trials (n<80 for each trial), which compared daily supportive text messages plus treatment as usual with treatment as usual alone for the management of patients with MDD, a sample size of 80 is estimated to have sufficient power for the current protocol. Allowing for a projected maximal 20% overall dropout rate, we propose to recruit 100 patients with MDD into the trial, with 50 patients randomly allocated into each study arm.

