### Effectiveness Evaluation

#### Hypothesis

As the same messages will be delivered through the supportive text message program and the email program, we hypothesize that daily email messaging will not be inferior to daily supportive text messaging in reducing depression symptoms and improving quality of life for patients with MDD. We further hypothesize that participant dropout rates and satisfaction rates will be comparable in the two arms of the study.

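### The power claim for 80 patients rests on text versus usual care, a contrast this trial does not contain, and so does not support the noninferiority comparison of email with text

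*Protocol article*

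**What the plan says.** The Sample Size section gives its basis openly: "Based on the effect sizes (Cohen *d* of 0.85 and 0.67) achieved in 2 previous randomized trials", trials "which compared daily supportive text messages plus treatment as usual with treatment as usual alone for the management of patients with MDD". From this it concludes that "a sample size of 80 is estimated to have sufficient power for the current protocol". It then adds the dropout allowance ("Allowing for a projected maximal 20% overall dropout rate, we propose to recruit 100 patients with MDD"), "with 50 patients randomly allocated into each study arm".

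The Study Design section defines the protocol to which that claim applies: "This study is a randomized noninferiority trial testing the outcomes for email messaging", with text messaging as the comparator. The Hypothesis section agrees: "we hypothesize that daily email messaging will not be inferior to daily supportive text messaging in reducing depression symptoms", on the reasoning that both arms receive the same messages. Both arms also receive usual care, and no arm receives usual care alone.

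The Data Analyses section plans an ANCOVA with the baseline score as covariate. The article gives no margin, alpha, power target or baseline correlation, and nothing links the two effect sizes to a margin.

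**The concern.** A sample size is sufficient only for a stated comparison. The two effect sizes measure how much text messaging adds to usual care. The trial compares two active arms expected to perform alike, and its task is to exclude a loss of a given size with email. The power for that task depends on the loss to be excluded, and the effect of text over usual care does not supply it.

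A size that comfortably detects the whole benefit of text may be too small to show that email keeps a useful part of it. A reader who takes the power claim at face value may then read a nonsignificant difference as evidence of noninferiority, although the interval may be too wide to exclude a meaningful loss. This matters because the Conclusion section expects the result to bear on patient care and resource allocation.

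**Working it through.** **Inputs from the article.** d = 0.85 and 0.67, 80 evaluable (40 per arm), 20% dropout, 100 recruited (Sample Size); noninferiority of email to text (Study Design, Hypothesis); ANCOVA on baseline (Data Analyses).

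**Assumptions, not in the article.** True difference zero; one-sided alpha 2.5%, with 5% as an alternative; baseline correlation r of 0 (unadjusted), 0.5 or 0.7; margins in SD units, with half of each cited effect as a working example (0.67/2 = 0.335; 0.85/2 = 0.425). The article sets none of these.

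**Step 1: reproduce the stated size.** As a superiority comparison at two-sided 5%, with SE = √(2/40) = 0.2236 SD, the noncentrality is 0.67/0.2236 = 3.00 and 0.85/0.2236 = 3.80. By noncentral t on 78 df, power is 84% and 96%. The dropout step is exact: 80/(1 − 0.20) = 100. So 80 is adequate for detecting text over usual care at the cited effects.

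**Step 2: power for email versus text.** For a margin M and true difference zero, SE = √[(2/40)(1 − r²)], which is 0.2236, 0.1936 and 0.1597 SD for r = 0, 0.5 and 0.7. Power is the probability that a noncentral t with noncentrality M/SE exceeds the one-sided critical value.

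| One-sided alpha | r | Power at M = 0.335 | Power at M = 0.425 | M for 80% power |
|---|---|---|---|---|
| 2.5% | 0 | 32% | 47% | 0.63 SD |
| 2.5% | 0.5 | 40% | 58% | 0.55 SD |
| 2.5% | 0.7 | 54% | 75% | 0.45 SD |
| 5% | 0 | 44% | 60% | 0.56 SD |
| 5% | 0.5 | 53% | 70% | 0.49 SD |
| 5% | 0.7 | 67% | 84% | 0.40 SD |

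Eleven of the twelve power figures are below 80%. The exception needs r = 0.7, one-sided 5% and the larger margin together.

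**Step 3: what an 80%-power margin would concede.** Unadjusted at one-sided 2.5%, the margin is 0.634 SD. Then 0.634/0.85 = 75% and 0.634/0.67 = 95%: email could lose about three quarters of the larger cited effect, or nearly all of the smaller one, and still pass.

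**Step 4: expected precision.** The 95% CI half-width is 1.991 × SE: 0.45, 0.39 and 0.32 SD for r = 0, 0.5 and 0.7.

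**The case against.** The strongest reply is that noninferiority power is undefined without a margin and alpha. This is a condensed article, and the full protocol or analysis plan may hold both. A reader might infer from the figures above that the power claim is false. The documents do not support that: at a margin of 0.67 SD and one-sided 2.5%, 40 per arm gives 84% unadjusted and 93% with r = 0.5. What can be said is that the basis given does not support the claim. A margin recorded elsewhere would not repair that basis, because the Sample Size section derives the number from a different comparison.

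A reader might also infer that the trial is set to be inconclusive at any margin that keeps part of the text effect. That is too strong. At 0.425 SD with r = 0.5 and one-sided 2.5%, power is 58%, and with r = 0.7 it is 54% to 75% at the half-effect margins, so success is the likelier result there. The 80%-power margins in the table all lie below both cited effects, so each keeps some of the benefit.

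Nor does the article say that the whole effect serves as the margin, and that choice should not be attributed to it.

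Two further points stand. The planned analysis is ANCOVA, so the adjusted rows are closer to it than the unadjusted ones, although the correlation is unknown. Half-effect margins are a convention that the article does not set. Finally, the Discussion says that the findings will inform a larger multicenter trial. That makes a modest size reasonable, but it does not withdraw the power claim.

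**Conclusion.** The point holds as a mismatch between the power claim and the comparison it is made for. The arithmetic is sound for text against usual care, but that is not the question the trial asks, and nothing else in the article supplies a basis for email against text. Whether 80 is enough depends on a margin and alpha not given here. At half-effect margins, with a true difference of zero and baseline correlations up to 0.7, power runs from 32% to 75% at one-sided 2.5% and from 44% to 84% at one-sided 5%. It is therefore below 80% in nearly all of the cases examined. The paragraph should be corrected before it is relied on; the design itself need not change.

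**What to change.** In the Sample Size section, remove the statement of sufficient power as derived from the text-versus-usual-care effects. In its place, state what 80 completers deliver for email versus text: the expected 95% CI half-width (about 0.45 SD unadjusted, 0.39 SD with r = 0.5, 0.32 SD with r = 0.7) and the power at the chosen margin and alpha under the planned ANCOVA, with the assumed correlation given.

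If recruitment stays at 100, describe the effectiveness comparison as an estimate to inform the planned multicenter trial named in the Discussion, and claim noninferiority only if the confidence interval excludes the prespecified margin.

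The cost is one rewritten paragraph and a less favourable power statement. No extra patients are needed.
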